## 3. Discussion

Unilateral spatial neglect is a complex neurological syndrome with a high prevalence and adverse effects. In this study, we design a random and comparison clinical trial to observe the effectiveness of PA and EMT and combined therapy for USN of patients with poststroke.

A major consideration of this study is based on the theoretical model of Barrett et al. (21), who mentioned that stroke-induced unilateral spatial neglect can be characterized by visual–perceptual spatial neglect and motor intention deficits. Many studies have investigated the effectiveness of PA for USN, indicating that PA is a promising intervention to alleviate symptoms of neglect and improve functional outcomes. However, some contrary studies have shown that patients improved only motor-intentional deficits after PA intervention (45, 46). EMT is another effective intervention used in the study. Balslev and Odoj (47) supported the coupling of attention and gaze and argued that interventions on target gaze signals can alleviate visual–perceptual spatial neglect. Therefore, we hypothesized that the combination of the two interventions might both treat the patients' classic visual–perceptual spatial neglect and motor intention deficits, resulting in a more positive and comprehensive effect.

In contrast, although previous studies have explored PA in combination with other treatments, most studies have selected therapies with the same bottom-up approach (19, 20, 48). It is notable that the two interventions chosen for the present study stem from the following two different approaches: the “top-down” approach aims to improve perceptual and behavioral biases by acting on disrupted consciousness and thus on higher-level cognitive processes, and the “bottom-up” approach is a physiological approach that aims to influence sensory-motor levels through passive sensory manipulation or visuomotor adaptation. PA belongs to a bottom-up intervention approach, while EMT belongs to a top-down intervention approach. PA may ameliorate neglect symptoms by improving patients' spatial cognitive processes: recalibration and spatial alignment (49, 50), and imaging studies have shown that PA activates the parietal cortex and cerebellum associated with recalibration and spatial rearrangement (39, 51, 52), as well as altering the balance of activity in bilateral parietal, frontal, and temporal regions (53), and altering frontal-parietal, parietal-temporal, and cerebellar-parietal-hippocampal network connections in the resting state (54, 55). EMT improves spontaneous eye exploration and spatial attention to the space contralateral to the brain injury. An fMRI study showed that EMT induced alterations in brain activation in the striate and extrastriate cortex as well as in oculomotor areas (56). The two showed more differences in neural mechanisms, so the combined intervention of these two approaches may affect the broader brain network associated with USN. Based on this, we chose to combine these two approaches in the present study, which we hypothesized would have positive effects.

Since patients with USN themselves suffer from attention deficits and other cognitive dysfunctions, an unreasonable combination of therapies rather leads to an aggravation of neglect symptoms (48), and therefore, the selection of the combination of different interventions needs to take into account the relevant influencing factors and the patient's tolerance. Saevarsson et al. (19) and Choi et al. (20) combined an active engagement (PA) with a passively received (neck vibration or FES) intervention, both of which showed better efficacy of the combined intervention, but both interventions used in our trial required patients to actively participate, so this may be a limitation of this interventional approach. However, the few patients who completed the intervention described that they were able to accept the intensity of the training and did not experience any particular fatigue or difficulty accomplishing it.

There are other limitations to our study. (a) Our target population was set to patients with subacute stroke, and the efficacy of patients in the chronic phase was not discussed. (b) The efficacy of interventions with active engagement is influenced by cognitive level, and we only mentioned the ability to cooperate with the therapist in the eligibility criteria, discussed the overall efficacy, and did not stratify the analysis of the efficacy of patients with different cognitive levels. (c) Patients with severe USN were excluded from the study, so the efficacy for this group is not yet clear. (d) This is a preliminary exploratory study, and the follow-up time in this trial is only 2 weeks after the end of treatment.

We aimed to conduct a randomized controlled trial to investigate whether the PA combined with EMT has the potential to be a promising treatment option for poststroke USN. If this study provides positive results, it will be possible to recommend that these techniques be implemented in treatment protocols for patients with USN.

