### 2.9. Adverse events

A safety questionnaire will be administered to all participants prior to the administration of the first PA or EMT to reduce the risk of possible symptoms, including dry eyes, headache, and irritability, and will be recorded at the end of each session. Descriptive statistics will be provided for all adverse events.

The following measures will be taken to prevent these events: (a) prior to the intervention, the investigator will communicate adequately to ensure that the patient is in a good state after rest; (b) during the intervention, the investigator will closely monitor the patient's condition and keep records; (c) if the patient feels any discomfort, the intervention will be suspended immediately, the intervention protocol will be adjusted (by increasing the interval of rest), or the intervention will be stopped. If a serious adverse event occurs, we will seek professional evaluation, cover the cost of treatment for the adverse event caused by the trial, and provide some financial compensation.

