### 2.10. Dropout criteria

The intervention will be discontinued if the subject meets one or more of the following criteria: (a) the subject has poor compliance and fails to perform the treatment as required, e.g., the subject does not cooperate with the investigator or the subject does not come to treatment on time; (b) medical records are incomplete and affect efficacy or safety evaluation; (c) subject voluntarily withdraws; (d) subject experiences an adverse event (including episodes of ocular pain, headache, and irritability); and (e) the subject has a severely progressive disease or some comorbidity, complications, or specific physiological changes.

Patients who drop out will not be included in the efficacy analysis; if they drop out for reasons such as the occurrence of an adverse event, they will be included in the safety analysis.

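### Efficacy is limited to completers and a dropout's place in the safety analysis depends on the recorded reason for leaving, so a patient whose neglect worsens and who leaves can be absent from both results

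*Protocol article*

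**What the plan says.** Four parts of the protocol article bear on this.

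- **Efficacy set.** Section 2.10 states: "Patients who drop out will not be included in the efficacy analysis". The Abstract agrees, admitting to the final analysis only those who finished every treatment and assessment session.
- **Safety set.** The same sentence of section 2.10 goes on to admit dropouts to the safety analysis on a condition: that they left because of an adverse event or a comparable reason. Nothing is said of those who left for other reasons.
- **Adverse events.** Section 2.9 refers to "possible symptoms, including dry eyes, headache, and irritability, and will be recorded at the end of each session". It adds that "Descriptive statistics will be provided for all adverse events". Section 2.10(d) gives as one ground for discontinuation that the "subject experiences an adverse event (including episodes of ocular pain, headache, and irritability", among others. Neither section names worsening of neglect.
- **The hazard.** The Discussion says of patients with neglect that "an unreasonable combination of therapies rather leads to an aggravation of neglect symptoms". It therefore asks that tolerance be weighed when therapies are combined, and concedes that needing active participation in both components may be a limitation.

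Section 2.11 adds that as much data as possible will be collected from patients who discontinue or deviate. It does not tie those data to a named analysis.

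**The concern.** Worsening neglect is the harm that the protocol's own rationale links to badly chosen combinations. It is also a harm that could plausibly make a patient stop cooperating or withdraw. The efficacy rule removes that patient because they left. The safety rule brings them back only if the departure is attributed to an adverse event or something like it. If it is recorded as poor compliance (2.10(a)) or voluntary withdrawal (2.10(c)), and nobody has recorded the worsening as an adverse event, neither analysis contains the patient.

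The stake is the credibility of a favourable result. The Discussion says that positive findings would support recommending these techniques in treatment protocols. A report that the combination works and is well tolerated would then rest on sets from which some of the relevant failures may have been removed by a coding decision. The therapist and the patient both know the assigned group (section 2.5), so coding of the reason for leaving cannot be assumed independent of arm.

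**Working it through.** **1. Tracing a worsened patient through the stated rules**

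| What happens to the patient | Efficacy analysis | Safety analysis |
|---|---|---|
| Completes all sessions and assessments | Included, on BIT-C and CBS | Covered by the general promise in 2.9 |
| Leaves, reason recorded as an adverse event (2.10(d)) | Excluded | Included |
| Leaves as poor compliance or voluntary withdrawal (2.10(a), (c)), worsening recorded as an adverse event | Excluded | Unclear: 2.9 covers all events, 2.10 looks to the reason for leaving |
| Leaves as poor compliance or voluntary withdrawal, worsening not recorded | Excluded | Not included by the 2.10 rule |

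Only the last row is a full disappearance. The third row is an ambiguity between 2.9 and 2.10 that the same fix resolves.

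**2. How many patients the rule could touch**

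Inputs from section 2.4: 20 needed per group, 10% dropout, 22 per group, 88 in total.

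- The plan's figure: 20 × 1.10 = 22 per group, and 4 × 22 = 88.
- Planned dropouts: 22 − 20 = 2 per group, and 88 − 80 = 8 overall.

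Assume that both combined-arm dropouts leave under (a) or (c) and that any worsening goes unrecorded. The documents give no rate of worsening, so the full range is shown.

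| Combined-arm dropouts who worsened (assumed) | True proportion | What the analysed patients show |
|---|---|---|
| 0 | 0/22 = 0% | 0/20 |
| 1 | 1/22 = 4.5% | 0/20 |
| 2 | 2/22 = 9.1% | 0/20 |

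No completer is assumed to worsen in this illustration.

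**3. The matching effect on the efficacy mean**

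Inputs from section 2.4: mean pilot BIT-C change of 39.33 (combined) and 26.33 (EMT), a difference of 39.33 − 26.33 = 13.00. Assume that the 20 completers average 39.33, that the 2 dropouts change by c, and that the EMT group stays at 26.33.

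Mean over all randomised = (20 × 39.33 + 2c) / 22 = (786.6 + 2c) / 22

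| c (assumed) | Mean over all 22 | Completer mean too high by | Difference from EMT |
|---|---|---|---|
| 0 | 786.6/22 = 35.75 | 3.58 | 9.42 |
| −10 | 766.6/22 = 34.85 | 4.48 | 8.52 |
| −20 | 746.6/22 = 33.94 | 5.39 | 7.61 |

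The values of c are illustrations and are not estimates from the trial. They show that two patients in an arm of 22 can matter against a planned difference of 13 points.

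**The case against.** The case on the other side is substantial, and much of it stands.

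- **A reader might infer that safety capture is confined to eye symptoms, headache and irritability.** The text does not support that. Both lists are introduced as examples, 2.9 promises to describe every adverse event, and it says that "the investigator will closely monitor the patient's condition and keep records". Nothing bars recording worsened neglect or fatigue. That 2.9 and 2.10 give different examples is no contradiction, and adding particular questionnaire items would be preference.
- **A reader might infer that deterioration goes unmeasured.** It does not. BIT-C and CBS are the primary outcomes, taken at baseline and at two later times by an assessor blinded to group. A patient who worsens and completes counts against that arm, although only through a group comparison.
- **A reader might infer that the protocol expects this combination to aggravate neglect.** The Discussion speaks of an ill-chosen combination and argues that pairing a top-down with a bottom-up approach is well chosen. Its remark that "the few patients who completed the intervention described that they were able to accept the intensity of the training" comes from a group selected for finishing, but it is commentary and no planned analysis depends on it.
- **Data from leavers are to be collected under 2.11.** This is true and useful, but no analysis there restores the patients whom 2.10 removes.
- **Disappearance needs several conditions together:** dropout, a particular coded reason, and no adverse event recorded. This is correct, and it limits the size of the problem.

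The rule itself remains. Section 2.10 does not merely leave the safety set to a later document. It states a criterion, and that criterion turns on the reason for leaving.

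**Conclusion.** The concern holds in a limited form. Followed as written, section 2.10 and the Abstract allow a patient whose neglect worsens, and who leaves for a reason not labelled an adverse event, to be absent from both efficacy and safety results. This is a stated rule that can bias the reporting of harm, and it should be changed before analysis.

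At the planned dropout it reaches about 2 patients per arm and 8 overall, fewer to the extent that dropouts are coded as adverse events and more if dropout exceeds 10%. In the combined arm that is a worsening proportion of up to 9.1% seen as zero, and a completer mean too high by 3.6 to 5.4 BIT-C points if both dropouts changed by between 0 and −20. These figures rest on assumed outcomes for the dropouts. The documents give no evidence that worsening will occur, or that it will be miscoded.

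**What to change.** 1. In section 2.10, replace the reason-dependent rule with a safety set of all patients who started their assigned care, including conventional rehabilitation in the control arm, whatever their reason for leaving.
2. State that worsening of neglect is reported as a safety outcome.
3. Tabulate by arm, at T1 and at T2, the number and percentage of patients with BIT-C below or CBS above their own baseline. Use the scores already collected and any obtained after discontinuation under section 2.11. Show beside them, by arm, the number with no post-baseline score.

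The cost is a short change of text and one table, with no new instrument. There are two limits. With no threshold for decline, some flagged changes will be test-retest noise, which the control arm helps to gauge. The schedule in Table 1 has no assessment at withdrawal, so patients who leave before T1 may have baseline scores only. The count of missing scores at least makes them visible.

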#### 2.2.2. Exclusion criteria

a) Severe cognitive impairment (MMSE <16) and non-cooperation.b) Severe USN (star cancellation tests <8).c) Severe non-spatial attention deficit (digital checking method).d) Patients with severe organ diseases.e) Inability to comply with the time frame of this study.f) Unsigned informed consent.

All subjects will sign an informed consent document before undergoing any study procedures.

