### 2.7. Baseline data

Baseline data are collected after informed consent and before randomization. The baseline assessment includes demographic characteristics such as sex, age, time of onset, cause of damage, and assessment scales including the Mini-Mental State Examination, Catherine Bergego Scale, Behavioral Inattention Test-Conventional Subset (BIT-C), and Modified Barthel Index (MBI). All baseline data will be collected *via* paper forms.

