#### 2.8.1. Mini-mental state examination

The Chinese version of the MMSE was initially developed by Katzman et al. (40) and later widely used in clinical practice and studies. The test includes cognitive assessments in five domains: time and place orientation, memory, attention and calculation, immediate and long-term memory, and language and comprehension. The total score of the test is 30, and the cutoff points for dementia screening are 16/17 for illiterate, 19/20 for those with 1–6 years of education, and 23/24 for those with 7 or more years of education (41).

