### 2.12. Data analysis

IBM SPSS Statistics for Windows, Version 26.0 (IBM Corp., Armonk, NY, United States) will be used for statistical analysis. 2-tailed *P* < 0.05 will be considered a statistically significant difference. Continuous variables will be expressed as mean with standard deviation or median with interquartile range, whereas categorical data will be expressed as counts and percentages. Baseline comparisons will be used to examine potential differences between 4 groups. Age, time of onset, and MMSE will be analyzed by ANOVA or Kruskal-Wallis test. Sex, cause of damage will be measured using Chi-square tests. The Kolmogorov-Smirnov test will be used to evaluate the normality of distributions. If a normal distribution is confirmed, one-way ANOVA will be used to examine the effectiveness of intervention between the 4 groups at T1, T2, with Bonferroni correction for multiple comparisons as a *post hoc* test. Otherwise, Kruskal-Wallis (non-parametric test) will be used.

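### Baseline MMSE is collected but left out of the efficacy model, although the protocol says cognition influences response: a modest loss of precision, not a bias

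*Protocol article*

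**What the plan says.** Protocol article, section 3 (Discussion), limitation (b): "The efficacy of interventions with active engagement is influenced by cognitive level". The same limitation adds that the authors "did not stratify the analysis of the efficacy of patients with different cognitive levels". The preceding paragraph says that both trial interventions need the patient's active participation, so the statement applies to PA, EMT and the combination.

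On the range of cognition admitted, section 2.2.2 excludes "Severe cognitive impairment (MMSE <16) and non-cooperation", and section 2.8.1 says "The total score of the test is 30". Scores from 16 to 30 can therefore enter.

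On timing, section 2.7 lists MMSE among the baseline assessments and says "Baseline data are collected after informed consent and before randomization". Section 2.5 allocates from a single ranked list of 88 random numbers, with no stratification.

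On analysis, section 2.12 names MMSE once, in the baseline comparison of the four groups: "Age, time of onset, and MMSE will be analyzed by ANOVA or Kruskal-Wallis test". For efficacy, "one-way ANOVA will be used to examine the effectiveness of intervention between the 4 groups at T1, T2", "with Bonferroni correction for multiple comparisons" as the post hoc step, and Kruskal-Wallis if normality is not confirmed. No covariate appears in either branch.

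**The concern.** The protocol names a characteristic that it believes influences response, measures it at a time when it is a valid covariate, does not balance it in the allocation, and then fixes an efficacy test that cannot use it. A significance test of MMSE at baseline does not fill the gap. It adjusts nothing, and under proper randomisation it tests a null hypothesis already known to be true.

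This is not detail that an article leaves to a fuller analysis plan. Section 2.12 names the efficacy test, and a one-way ANOVA has no place for a covariate.

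What is at stake is efficiency. If MMSE predicts the outcome, the variation it explains stays in the residual, and any chance difference in cognition between arms stays in the estimates from this trial. That matters most for combined versus EMT, the comparison that set the sample size.

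**Working it through.** **Inputs from section 2.4.** BIT-C change: combined 39.33 (SD 18.717), EMT 26.33 (SD 7.638), PA 20 (SD 2.828). Alpha 0.05, two-sided by section 2.12; beta 0.2. Stated need: 20 per group for combined versus EMT and 9 per group for combined versus PA.

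**Step 1: reproduce the plan's figure.** Two-sample t-test, pooled SD = sqrt((s1² + s2²)/2), noncentral t.

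- Combined versus EMT: difference 39.33 − 26.33 = 13.00; pooled SD = sqrt((18.717² + 7.638²)/2) = 14.29; d = 13.00/14.29 = 0.909. Power is 77.9% at 19 per group and 80.0% at 20, so 20 is needed.
- Combined versus PA: difference 19.33; pooled SD 13.39. Power is 76.6% at 8 per group and 82.0% at 9, so 9 is needed.

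Both stated figures reproduce exactly, with no covariate assumed.

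**Step 2: is the unadjusted analysis biased?** Simulation with four arms of 20, no treatment effect and 20,000 runs gave a type I error of 0.051 (MMSE–outcome correlation r = 0.3) and 0.049 (r = 0.5). The mean difference between two arms was about 0 in both. The unadjusted ANOVA is valid.

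**Step 3: precision given up.** A covariate with correlation r multiplies residual variance by 1 − r², so the effective standardised difference is 0.909/sqrt(1 − r²). The documents give no r; the values below are assumptions. Power is for combined versus EMT at 20 evaluable per arm, two-group pooled t. Alpha 0.05/6 reads the Bonferroni step as covering all six pairs of arms.

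| Assumed r | Residual variance | Power, alpha 0.05 | Power, alpha 0.05/6 |
|---|---|---|---|
| 0 | 100% | 80.0% | 54% |
| 0.2 | 96% | 81.6% | 56% |
| 0.3 | 91% | 83.6% | 59% |
| 0.4 | 84% | 86.4% | 64% |
| 0.5 | 75% | 89.9% | 70% |

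At r = 0.2 to 0.3 the gain is about 2 to 4 points at alpha 0.05 and about 2 to 5 points at 0.05/6. With Welch's test, which allows for the unequal SDs, the range from r = 0 to r = 0.5 is 79% to 89% at 0.05 and 52% to 67% at 0.05/6. The conclusion is the same.

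**Step 4: chance imbalance.** The difference in mean MMSE between two arms of 20 has standard error SD × sqrt(2/20) = 0.316 × SD, so a 95% range of about ±0.62 SD. For an assumed MMSE SD of 3, 4 or 5, the arms differ by 2 points or more in 3.5%, 11% or 21% of trials.

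On the outcome scale, with MMSE SD 4, a 2-point imbalance shifts the BIT-C difference by r × (14.29/4) × 2. That is 1.4 points at r = 0.2 and 3.6 points at r = 0.5. The planned difference is 13 points, with standard error 14.29 × sqrt(2/20) = 4.5.

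**The case against.** **The choice is disclosed, and an overall effect is a legitimate target.** Limitation (b) says that overall efficacy is discussed, and limitation (d) calls the study preliminary and exploratory. This stands as far as subgroup or interaction analysis goes: the absence of one is not an error. It does not answer the covariate point, because adjustment also serves the overall comparison and is never mentioned.

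**A reader might infer that omitting MMSE biases the comparison or makes its p-values untrustworthy.** The documents do not support that. Under randomisation, chance differences in cognition are already counted in the ANOVA standard error, as Step 2 shows. Step 4 adds that even a fairly unusual imbalance shifts the result by less than one standard error.

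**A reader might also infer that the protocol names MMSE as a modifier of the treatment effect, or calls the gap unavoidable.** It does neither. It speaks of cognitive level, of which MMSE is the measure collected, and it only lists the missing analysis as a limitation. Nor would a common-slope covariate address effect modification. An arm-by-MMSE term would, but it has 3 degrees of freedom with about 20 patients per arm and would be imprecise.

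**The benefit is assumed.** This stands. No correlation is given, and the upper figures depend on r near 0.5. If MMSE and baseline BIT-C overlap, MMSE adds less once baseline BIT-C is in the model. Excluding non-cooperation and severe non-spatial attention deficit (section 2.2.2) may narrow the cognitive spread. The education-specific cut-offs in section 2.8.1 suggest that the raw score partly reflects schooling. Each could lower r; none makes the covariate invalid.

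**Conclusion.** The point holds as a modest, inexpensive improvement. The plan collects a valid baseline covariate that its own reasoning marks as relevant, and fixes an efficacy test that cannot use it. The cost is lost precision and no adjustment for chance imbalance in cognition; validity is not affected.

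The power ranges in the brief rest on the pilot means and SDs in section 2.4, 20 evaluable patients per arm, a correlation that is the same in both arms, and r between 0.2 and 0.5, for which the documents give no basis. The lower end should be taken as seriously as the upper, with some further shrinkage likely once the outcome's own baseline is adjusted for. The gain is somewhat larger under the Bonferroni step that the plan actually specifies, where the unadjusted power is low.

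**What to change.** - In section 2.12, replace the one-way ANOVA at T1 and T2 with a pre-specified linear model (ANCOVA) for each outcome: arm, baseline value of that outcome, and baseline MMSE as a continuous covariate, with Bonferroni-adjusted contrasts between arms.
- Replace the Kruskal-Wallis fallback, which cannot carry covariates, with a method that can, for example rank-based ANCOVA, or the same linear model with robust or bootstrap standard errors.
- Report baseline MMSE by arm descriptively instead of testing it.
- Optionally, add one arm-by-MMSE interaction, labelled exploratory and reported as estimates with 95% confidence intervals.
- Reword limitation (b) to match the new analysis. It also says that eligibility refers only to ability to cooperate, whereas section 2.2.2 sets an MMSE limit; the two should be reconciled.

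MMSE costs one degree of freedom, and the change brings slightly more analysis work. No new data are needed. The article reports recruitment as ongoing, so on its account the change can be made before the data are analysed.
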